### Type of Liver Injury

Three indicator variables will be defined for each type of liver injury (hepatocellular, cholestatic and mixed). When a type of liver injury is present at a subset of time points, the indicator variable will be set to “Present”.

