### Type of liver injury

A liver injury can be categorized as either hepatocellular, cholestatic or mixed type of injury as established in the international consensus meeting criteria (Benichou 1990) based on the ratio (R) of results of serum ALT to ALP relative to their upper limit of normal (ULN). Thus, the R ratio = (ALT/ ULN) / (ALP/ ULN). An R ratio > 5 denotes hepatocellular and < 2 cholestatic injury. Ratios between 2 and 5 are categorized as mixed hepatocellular-cholestatic injuries.

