### Time-points of evaluation and samples management

Patients will be evaluated and will have blood sample collection: Ideally 9 samples [baseline (day 0), day 1, day 3, week 1, week 2, week 3, week 4, week 8 and week 12] and at least 3 mandatory samples (baseline, between day 5 and week 2, and between week 4 and week 12). Baseline will be defined as the day of first SAFE-T sample. The sample volume required for measuring the biomarkers is 24 ml of blood at each time-point: 10ml of blood in a dry tube, 5 ml in EDTA tube, 5ml in Li-Heparin tube and 4ml tube containing hexokinase inhibitor. The total amount of blood drawn will be 216 ml in three months in addition to routine tests (168 ml in outpatients). The potential risk of sample collection is phlebitis. This can be a local inflammation or in very rare cases, it can lead to a systemic infection. In addition 15 ml of urine will be sampled.

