### Subgroups and Special Populations

The recovery outcome for each type of DILI (cholestatic, hepatic or mixed) will be investigated separately. The biomarkers that have the highest AUROC estimates will be qualified as good predictors of recovery outcome for the particular type of DILI that is being investigated. Biomarker thresholds will also be calculated for each type of liver injury.

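### The type-of-injury indicators count any visit, so falling ALT can add mixed and cholestatic labels to a patient who presented as hepatocellular

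*Protocol*

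**What the plan says.** Protocol section 6.3.3, under the secondary binary endpoints, states: "Three indicator variables will be defined for each type of liver injury (hepatocellular, cholestatic and mixed"). It then gives the rule across visits: "When a type of liver injury is present at a subset of time points, the indicator variable will be set to" present. It names no reference visit, no minimum number of visits and no rule that a patient can have only one type.

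Section 3.6.1 supplies the classification. "Thus, the R ratio = (ALT/ ULN) / (ALP/ ULN"). "An R ratio > 5 denotes hepatocellular and < 2 cholestatic injury", and "Ratios between 2 and 5 are categorized as mixed hepatocellular-cholestatic injuries". It does not say at which visit R is taken, or that either enzyme must still be abnormal.

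Section 3.6.3 sets the visits: "Ideally 9 samples [baseline (day 0), day 1, day 3, week 1, week 2, week 3, week 4, week 8 and week 12"], with "at least 3 mandatory samples (baseline, between day 5 and week 2, and between week 4 and week 12"). Its data collection list includes ALT and ALP at every time-point, so R can be computed at each visit up to W12.

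Type is used in two ways. Section 2.2 makes it outcome (iii), for which the best biomarkers and thresholds are to be found, and section 7.1 applies ROC analysis to each binary outcome. Section 7.4 uses it for subgroups: "The recovery outcome for each type of DILI (cholestatic, hepatic or mixed) will be investigated separately".

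Section 3.6 (Methods) also sets an ALP cut-off of 2xULN for cholestatic cases, without saying whether it applies to entry, to classification or to both.

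**The concern.** R compares two enzymes and does not measure whether injury is present. In a patient who starts with high ALT and modest ALP, recovery lowers R. On the way down R can pass through the mixed band and end in the cholestatic band, although the nature of the injury has not changed. Because 6.3.3 counts a type seen at some of the visits, these later values add labels to the patient.

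Two consequences follow for outcome (iii). First, the mixed and cholestatic indicators depend partly on whether ALT resolved, so a biomarker that tracks resolution could appear to predict cholestatic injury. Second, they depend on how often the patient was sampled, which may be anywhere from three to nine times. If 7.4 used the same indicators, its subgroups would overlap and would be defined partly by the recovery that they are meant to help predict.

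**Working it through.** The protocol gives no figure for the share of patients with each type or with several types, so there is nothing to reproduce. The check has three parts.

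**1. Arithmetic on the protocol's own cut-offs.** With ALT and ALP in multiples of ULN, R = ALT/ALP.

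- R falls to 5 or below when ALT ≤ 5 × ALP, and below 2 when ALT < 2 × ALP.
- Full recovery (section 1.6.1) needs ALT < 2xULN. With ALP at 1xULN or above, every such patient has R < 2/1 = 2 and is labelled cholestatic.
- With lower ALP the label needs lower ALT: below 1.4xULN when ALP is 0.7xULN (2 × 0.7), and below 1.0xULN when ALP is 0.5xULN (2 × 0.5).
- Two normal values can produce the label: ALT 0.5 and ALP 0.6 give R = 0.5/0.6 = 0.83.

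**2. One illustrative patient (assumed values).** At d days after D0, ALT = 0.5 + 19.5 × 0.5^(d/7) and ALP = 0.7 + 0.8 × 0.5^(d/21).

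| Visit | ALT (xULN) | ALP (xULN) | R | Label |
|---|---|---|---|---|
| D0 | 20.0 | 1.50 | 13.3 | hepatocellular |
| W1 | 10.25 | 1.33 | 7.7 | hepatocellular |
| W2 | 5.38 | 1.20 | 4.5 | mixed |
| W3 | 2.94 | 1.10 | 2.7 | mixed |
| W4 | 1.72 | 1.02 | 1.7 | cholestatic |
| W8 | 0.58 | 0.83 | 0.7 | cholestatic |
| W12 | 0.50 | 0.75 | 0.7 | cholestatic |

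D1 and D3 give R of 12.3 and 10.5, both hepatocellular. On the full schedule all three indicators are set. If this patient gives only the three mandatory samples, the result depends on their dates. Samples at D0, W1 and W4 set hepatocellular and cholestatic, while D0, W2 and W8 set all three.

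**3. Simulation of patients hepatocellular at D0 (R > 5).** All inputs are assumptions:

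- D0 ALT median 15xULN and ALP median 1.3xULN;
- late ALT 0.5 or 1.0xULN, and late ALP 0.5, 0.7 or 0.9xULN;
- ALP half-life 21 days, and 10% measurement noise after D0;
- mandatory visits placed at days 0, 10 and 56.

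A type counts as present if seen at any visit, and no ALP cut-off is applied. Ranges run over the late ALT and ALP levels and, in the first row, over half-lives of 5 and 10 days.

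| Median ALT half-life | 9 visits: mixed added | 9 visits: cholestatic added | 9 visits: both | 3 visits: at least one | 3 visits: both |
|---|---|---|---|---|---|
| 5–10 days | 91–97% | 51–99% | 49–91% | 85–100% | 15–41% |
| 20 days | 66–82% | 19–57% | 18–53% | 48–70% | 3–10% |
| 40 days | 27–52% | 3–16% | 3–15% | 14–33% | under 2% |

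The link to outcome is direct. With nine visits and a 10-day half-life, the cholestatic flag is set in 59–97% of patients whose last ALT is below 2xULN, and in 0–14% of the rest.

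**The case against.** The best counter-argument is the ALP cut-off of 2xULN for cholestatic cases in section 3.6. It cites the same consensus report as 3.6.1. If it belongs to the classification, the patient above is never cholestatic, because ALP peaks at 1.5xULN, and many false cholestatic flags in the simulation would go. This stands as far as it reaches. But the sentence can also be read as an entry threshold, since section 3.2 uses the same ALP value for inclusion. It also leaves the mixed flags untouched.

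One may add that 3.6.1 classifies a liver injury, so visits below the inclusion thresholds should not count. The protocol does not say so, and the mixed flags would not all disappear. If ALP stays above 0.6xULN, R reaches 5 while ALT is still above 5 × 0.6 = 3xULN. The patient above is mixed at W2 with ALT 5.38xULN.

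Separate indicators that may overlap are also a deliberate choice, and section 7 leaves statistical methods to the SAP. However, the visit rule is stated in the endpoint section and is not deferred.

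A reader might infer that most hepatocellular patients acquire all three types and that the endpoint is therefore meaningless. The documents do not support that. They give no kinetics, and the simulated share with both extra flags runs from 3% to 91% with nine visits. The simulation says nothing about patients who are mixed or cholestatic at D0. The hepatocellular indicator still identifies patients who had R above 5 at some visit. A reader might also infer that the 7.4 subgroups overlap in this way, but 7.4 does not say which visit or variable defines them.

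**Conclusion.** The concern holds in a limited form. As written, 6.3.3 and 3.6.1 let one patient collect several types as ALT falls. The mixed and cholestatic indicators then reflect recovery and attendance as well as the pattern of injury. That mechanism follows from the protocol's own cut-offs and needs no assumed kinetics.

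Its size does need them. Fast resolution and full attendance give heavy overlap; slow resolution or three visits give much less. All the simulated cholestatic figures also assume that the ALP cut-off in section 3.6 is not part of the classification, so they would be lower if it is. For 7.4 the supportable statement is conditional: its classification is not fixed, and if it borrows the 6.3.3 indicators, its subgroups will overlap and depend on outcome.

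The effect is confined to secondary outcome (iii) and possibly the subgroup analyses. The primary endpoint, full recovery at W12, does not use type.

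**What to change.** - In 6.3.3, define one mutually exclusive type per patient from R at D0. Alternatively, take R at the first sample that meets inclusion criterion 1 and has both ALT and ALP, with D0 as the fallback.
- State in 7.4 that the subgroups use this same classification.
- Report later R values descriptively only.
- Reconcile the ALP cut-off in section 3.6 with 3.6.1 and 6.3.3 by saying whether it belongs to the classification. If it does, say how a sample with R below 2 and lower ALP is handled.

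Anchoring at one sample gives each patient a single class, so overlap is zero by construction. D0 uses data already collected. The earlier anchor will often be unavailable, because section 1.7 expects measurements before D0 to be mostly ALT and total bilirubin; the fallback therefore has to be written down. Since criterion 1 may be met up to four weeks before baseline, R at D0 may already have fallen in some patients, which is the argument for allowing the earlier sample.

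The cost is a short text change with two consequences. A change of type during follow-up is no longer an endpoint, and objective 2.2(iii) becomes classification of the type at presentation rather than prediction over the 12 weeks.

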### Secondary Endpoints: Time to Events

The time from D0 to reaching the following outcomes will be calculated:

1. Full Recovery from DILI;
2. Severe biochemical DILI
3. Severe clinical DILI (i.e. death or liver complications/failure).

Where a patient does not meet the criteria of the outcome, a censored time will be used as the time of last follow-up visit.

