### Secondary Objectives

The new biomarkers will be compared to ALT and total bilirubin, which are the "Standard of Diagnosis" (including Hy's Law), and to ActiTest which is already commercially available for the secondary objectives:

- - - Investigate the performance of investigational biomarkers from baseline D0 to Week 12) to predict:

1. A subsequent increase in total serum bilirubin of at least 10 umol/l more than the baseline value (D0) or an elevation of total bilirubin to 34 umol/l (Hy's law is TBILI 2xULN together with ALT 3xULN) at any other measurements between D1 to W12;
2. Death or severe liver complications (including transplant and complications associated with liver failure such as: hepatic encephalopathy, hemorrhage, associated liver failure complications: kidney failure, medical ventilation, circulatory dysfunction and infections.
3. Type of liver injury (hepatic, cholestatic and mixed).
4. Time to discharge from hospital.
   - - For each of the outcomes in (i) to (iii) determine the best investigational biomarker with associated thresholds.
     - For each of the outcomes in (i) to (iii) determine the best combination of biomarkers with associated threshold.
     - Type of drugs suspected in DILI will be assessed.
     - The prevalence of associated liver risk factors such as alcohol consumption, metabolic factors, history of familial liver disease, history of drug adverse events, history of recreational drugs (cocaine, ecstasy, amphetamines), combination of different drugs and herbals will be assessed and may be incorporated into statistical models.

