### Patients and Methods

- 1. **Patients**

A total of 500 patients with acute DILI will be included. The duration of follow-up per patient will be 12 weeks.

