### Endpoints

### Primary Endpoint: Binary Recovery Outcome

The primary endpoint is the category 1 recovery outcome (see Section 1.6.1), that is the "full" recovery at the last visit (W12).

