### Severe Biochemical DILI

A patient will be deemed to have “severe biochemical DILI” if the patient has:

- An increase in total serum bilirubin of at least 10 umol/l more than the baseline value (D0); or
- An elevation of total bilirubin to 34 umol/l (Hy's law) at any other measurements between D1 to W12;

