### Severe Clinical DILI

- Dies of any cause
- Requires a transplant
- Complications associated with liver complications/failure such as: hepatic encephalopathy, hemorrhage, kidney failure, medical ventilation, circulatory dysfunction and infections.

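### Time to severe clinical DILI has no shared cut-off for events and censoring, so early last visits can bias hazards upward and can bias marker hazard ratios

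*Protocol*

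**What the plan says.** Protocol Section 6.4 times three outcomes from D0: full recovery, severe biochemical DILI and severe clinical DILI. One censoring rule serves all three. Where a patient does not meet the outcome, "a censored time will be used as the time of last follow-up visit". The rule sets a stopping time for patients without the event. It says nothing about when events stop being counted.

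The outcomes differ in how they are observed:

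- Severe biochemical DILI (Section 6.3.1) is read from laboratory values, with the bilirubin elevation sought "at any other measurements between D1 to W12".
- Severe clinical DILI (Section 6.3.2) is met if the patient "Dies of any cause", needs a transplant or has liver-related complications. Section 6.4 summarises it as "Severe clinical DILI (i.e. death or liver complications/failure"). Neither section ties it to a visit or gives a window.

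On follow-up, Section 3.1 states: "The duration of follow-up per patient will be 12 weeks". Section 3.6.3 describes nine samples as ideal but requires only "at least 3 mandatory samples (baseline, between day 5 and week 2, and between week 4 and week 12"). Section 1.6.1 gives an example of a data rule for the SAP: patients who die, withdraw or discontinue leave the Main Analysis Set and stay in the Full Analysis Set. Section 7.5 plans a survival model with time-dependent biomarker covariates for each time-to-event endpoint.

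**The concern.** For a laboratory outcome, the last visit is the last time the status is known, so censoring there is right. A death, transplant or complication can occur and become known between visits or after the last one, and a death always follows the last attended visit.

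Take two patients who meet the sampling minimum and are last seen at week 4. One dies in week 10, meets the outcome, and stays in the risk set until week 10. The other survives and is censored at week 4. Time at risk then depends on the outcome, which breaks the independent-censoring assumption of the survival model. The denominators after week 4 are too small and the hazard is too high. If the share of early last visits also differs by biomarker level, the comparison of hazards between levels is affected too. That comparison is the purpose of Section 7.5 for this endpoint.

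**Working it through.** The protocol gives no event rate, hazard ratio or expected number of events for this endpoint, so there is no stated figure to reproduce. The inputs below are assumptions, apart from the 12-week follow-up (Section 3.1) and week 4 as the earliest compliant last mandatory sample (Section 3.6.3).

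**Step 1: effect on 12-week risk.** Assume a constant hazard, a true 12-week risk of 10%, all events known to week 12, and a share f of patients with a last visit at week 4, the rest at week 12.

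- Survival to week 4: 0.90^(4/12) = 0.9655.
- Patients with an event between weeks 4 and 12: 0.9655 − 0.9000 = 0.0655. All stay in the risk set.
- Event-free patients still at risk after week 4: (1 − f) × 0.90.
- Estimated survival from week 4 to week 12: (1 − f) × 0.90 / [(1 − f) × 0.90 + 0.0655].
- Estimated 12-week risk: 1 − 0.9655 × that ratio.

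| f (assumed) | Event-free at risk | Ratio | Estimated risk (true 10%) |
|---|---|---|---|
| 0% | 0.900 | 0.9322 | 10.0% |
| 20% | 0.720 | 0.9166 | 11.5% |
| 30% | 0.630 | 0.9058 | 12.5% |
| 50% | 0.450 | 0.8730 | 15.7% |

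**Step 2: effect on the hazard ratio.** Assume a binary baseline marker split 50/50, a 12-week risk of 5% in the low-marker group and a true hazard ratio of 3. For group g with hazard h_g, event density is h_g·exp(−h_g·t). The number at risk is exp(−h_g·t) up to week 4, and exp(−h_g·t) − f_g·exp(−12·h_g) after it. The fitted log hazard ratio b sets the expected Cox score to zero: the sum over time of d1 − (d0 + d1)·n1·e^b/(n1·e^b + n0).

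| Last seen at week 4: low-marker / high-marker | Fitted hazard ratio (true 3) |
|---|---|
| 0% / 0% | 3.00 |
| 30% / 30% | 2.97 |
| 30% / 10% | 2.55 |
| 50% / 20% | 2.23 |
| 50% / 0% | 1.97 |
| 10% / 30% | 3.51 |

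**Step 3: check by simulation.** This used 400,000 patients per scenario, a true hazard ratio of 2, a low-marker risk of 5% or 10%, and Weibull shape 1 or 0.5.

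- Early last visits unrelated to the marker: a true risk of about 7.4% is estimated at 8.3–8.9% (25% last seen at week 4) and 10.2–11.8% (50%). The hazard ratio hardly moves, at 1.92–2.01 with up to 75% last seen early.
- Early last visits related to the marker: the hazard ratio is 1.56–1.71 for 50% of low-marker against 25% of high-marker patients, and 3.06–4.00 for 25% against 75%.
- Events and censoring both stopped at the last visit: the hazard ratio is 1.94–2.05, against 1.95–2.04 with complete follow-up. Where early last visits are unrelated to the marker, the risk is also recovered.

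The mismatch between the two stopping rules causes the bias. Early last visits alone do not. Steps 2 and 3 use a marker fixed at baseline, so they show direction and rough size, not the effect under the planned time-dependent covariates.

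**The case against.** The strongest reply is that the protocol never says that events after a patient's last visit are counted, and describes no tracing of patients beyond it. If events also stop at the last visit, this is ordinary right censoring and Step 3 shows no such bias. That is a fair reading for non-fatal complications. It does not work for death: nobody attends a visit after dying, so the rule would remove nearly every death from an endpoint that names death. As written, only patients without the event are cut at the last visit.

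A second reply is that the last visit is week 12. Section 6.1 speaks of "recovery at the last visit (W12"), Section 3.1 plans 12 weeks for everyone, and Section 2.2 lists death and severe complications under an objective worded "Investigate the performance of investigational biomarkers from baseline D0 to Week 12) to predict". This stands as the intention, and if all event-free patients attend week 12 there is no bias. But the sampling minimum and the provision for withdrawals both foresee earlier last visits.

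A third reply is that such detail belongs in the SAP. Much of it does, but the censoring rule is already fixed in Section 6.4, and a rule stated there needs correcting there.

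A reader might infer more than the documents support:

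- **That hazard ratios are distorted, and toward 1.** They move materially only if early last visits depend on the marker. No passage documents this, and the shift can go either way.
- **That outpatients have earlier last visits, because 168 ml is drawn instead of 216 ml.** At 24 ml per sample these are 7 and 9 samples. The protocol does not say which two are dropped.
- **That a reported absolute risk will be wrong.** Section 7.5 plans a model of the biomarker relationship and no 12-week risk estimate. The figures in Step 1 show the size of the upward bias in the hazard.
- **That both analysis sets are equally exposed.** Section 1.6.1 takes deaths out of the Main Analysis Set, along with withdrawn patients, many of whom would have early last visits.

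**Conclusion.** The point holds conditionally. Section 6.4 fixes the stopping time for event-free patients but not for clinical events, and Section 3.6.3 permits early last visits. The bias arises if some event-free patients are last seen before week 12 and later events in comparable patients become known and are counted. Hazards are then too high: on the assumptions of Step 1, a 10% risk reads as 11.5% to 15.7% when 20% to 50% are last seen at week 4. With equal early last visits across marker levels, the hazard ratio is almost unaffected (2.97 against 3). With unequal shares it ran from 1.97 to 3.51 in the cases shown in Step 2. The share last seen early, the event risk and the true hazard ratio are all assumed.

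The death component is affected in the Full Analysis Set only. Transplant and complications can be affected in both sets, less so in the Main Analysis Set. Severity is minor: one secondary time-to-event endpoint is concerned, and the primary endpoint is untouched.

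**What to change.** In Section 6.4, keep last-visit censoring for full recovery and severe biochemical DILI. For severe clinical DILI, add one sentence setting a single window: events count from D0 to day 84 (12 × 7 days), and event-free patients are censored on the date last known alive, transplant-free and complication-free, at most day 84. Take that date from records already collected or from a brief status check, and seek it in the same way for every patient who misses week 12. If only events are followed up, the mismatch returns. Carry the same wording into the SAP.

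The cost is one status date per patient, and a record check or short contact for those who miss week 12. Visits and samples do not change.

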# Statistical Methods

Statistical methods will be described in full in a statistical analysis plan (SAP).

Biomarkers and combinations of biomarkers will be assessed and selected using cross-validation on all of the data in the study.

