### Biomarker Assessment and Selection

Cross-validation using all of the data from the study will be used to assess and select biomarkers and combinations of biomarkers.

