### Specific Groups for Inclusion

The following groups can be included in the study but will not be included in the Main Analysis Set (see Section 5.1) but analyzed separately for the performance of new biomarkers versus ALT and total bilirubin:

- Patients with Amanita Phalloides intoxication;
- Patients with acute exacerbation of a previous non-active carrier of HBV or chronic hepatitis C due to an immunosuppressive drug;
- Patients with previous history of chronic liver disease with advanced fibrosis (at least septal fibrosis) due to non alcoholic liver disease (NAFLD, NASH) or alcoholic liver disease [excessive alcohol consumption (male > 30 g/day, female > 20 g/day)];

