### Patient Analysis Sets

- 1. **Main Analysis Set**

The Main Analysis Set is defined as the set of subjects who fulfilled the criteria as defined in the main inclusion criteria of the study, after confirmation by the

Adjudication Committee. Note that the special groups (see Section 3.3) included in the study are excluded from the Main Analysis Set.

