### Full Analysis Set

The Full Analysis Set (FAS) is defined as the set of subjects who were included into the study.

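### The protocol selects and assesses biomarkers on all study data, yet keeps the special groups and unconfirmed cases out of the Main Analysis Set

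*Protocol*

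**What the plan says.** Two places in the protocol fix the data for biomarker selection. Section 7, before its subsections, says: "Biomarkers and combinations of biomarkers will be assessed and selected using cross-validation on all of the data in the study". Section 1.6.3 consists of one sentence: "Cross-validation using all of the data from the study will be used to assess and select biomarkers and combinations of biomarkers". Neither names an analysis set.

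Section 3.3 lists three groups: Amanita intoxication, HBV or HCV exacerbation caused by an immunosuppressive drug, and previous chronic liver disease with advanced fibrosis. It says they "can be included in the study but will not be included in the Main Analysis Set" and are to be "analyzed separately for the performance of new biomarkers versus ALT and total bilirubin". Section 5.1 limits the Main Analysis Set to patients who meet the main inclusion criteria after Adjudication Committee confirmation, and adds: "Note that the special groups (see Section 3.3) included in the study are excluded from the Main Analysis Set". Section 5.2 defines the Full Analysis Set, which "is defined as the set of subjects who were included into the study".

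Section 1.6.1 bears on the repair. As an example of rules to be clarified in the SAP, it takes patients who die of any cause or withdraw out of the Main Analysis Set. It keeps them in the Full Analysis Set, classified by their last measurement.

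**The concern.** Choosing markers and estimating their performance against ALT and total bilirubin is the main output of the study. The protocol names one population for that work, all study data, and elsewhere directs that some of those patients be kept apart for the same purpose. An SAP author who follows sections 1.6.3 and 7 literally departs from sections 3.3 and 5.1, and the reverse also holds.

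The special groups may differ from the other patients in both marker level and recovery rate. A pooled AUROC then mixes prediction within the target population with differences between populations. Unconfirmed cases, in whom a marker may carry no information about recovery, can dilute a useful marker.

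**Working it through.** **1. The text, side by side.** The two instructions cover the same activity.

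| Patients | Sections 1.6.3 and 7 | Elsewhere in the protocol |
| --- | --- | --- |
| Section 3.3 special groups | in | outside the Main Analysis Set (3.3, 5.1); biomarker performance analysed separately (3.3) |
| Not confirmed by adjudication | in | outside the Main Analysis Set (5.1 only) |
| Deaths and withdrawals | in | outside the Main Analysis Set (1.6.1) |

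For the special groups the clash is direct: their data cannot be both pooled into the assessment of marker performance and analysed separately for it. For the other two rows it is a mismatch between the stated population and the set definition.

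**2. No figure to reproduce.** The protocol plans 500 patients but states no power, precision target, target AUROC or expected share outside the Main Analysis Set. What follows is illustration on assumed inputs.

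**3. Effect of pooling on an AUROC.** Assume a binormal marker with AUROC 0.75 in the target patients, 30% of whom do not recover. A share f of the total lies outside the Main Analysis Set. The pooled AUROC is the weighted mean, over all pairs of a non-recovered and a recovered subgroup, of Φ((difference in means)/√2), with weights equal to the products of the subgroup shares.

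- Scenario A: the marker is uninformative in the added patients, with the same marker level among those who recover and the same 30% non-recovery. The formula reduces to (1 − f) × 0.75 + f × 0.50. At f = 5% this is 0.7375, and at f = 10% it is 0.725.
- Scenario B: the marker behaves identically in both groups.
- Scenario C: uninformative, 60% non-recovery, level 1 SD higher.
- Scenario D: uninformative, 60% non-recovery, level 1 SD lower.
- Scenario E: AUROC 0.75 within the added patients, 60% non-recovery, level 1 SD higher.

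| f | A | B | C | D | E |
| --- | --- | --- | --- | --- | --- |
| 5% | 0.738 | 0.750 | 0.743 | 0.707 | 0.758 |
| 10% | 0.725 | 0.750 | 0.736 | 0.668 | 0.766 |
| 20% | 0.700 | 0.750 | 0.721 | 0.605 | 0.777 |
| 30% | 0.675 | 0.750 | 0.703 | 0.556 | 0.784 |

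Worked example, E at f = 10%:

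- The shift between non-recovered and recovered is 0.6745 × √2 = 0.954 SD.
- Non-recovered patients split 0.27 : 0.06 (shares 0.818 and 0.182). Recovered patients split 0.63 : 0.04 (shares 0.940 and 0.060).
- The four pairwise values are 0.750 (target vs target), 0.917 (added non-recovered vs target recovered), 0.487 (target non-recovered vs added recovered) and 0.750 (added vs added).
- The weighted sum is 0.577 + 0.157 + 0.024 + 0.008 = 0.766.

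**4. Cost in precision of restricting the set.** The width ratio is √(500/n): √(500/450) = 1.05 and √(500/400) = 1.12. With the Hanley–McNeil standard error, AUROC 0.75 and 30% non-recovery, the 95% half-width is 0.050 at n = 500, 0.052 at 450, 0.056 at 400 and 0.059 at 350.

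**The case against.** The strongest reply is that both sentences describe a validation scheme. Cross-validation on all the data most naturally means that no hold-out sample is set aside, and the specific rules in sections 3.3 and 5.1 would then govern who enters. That is a plausible intent, but the protocol does not state it. If it was meant, the repair only writes it down.

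It is also fair that assigning analyses to sets is usually SAP work, and section 7 defers full methods to the SAP. The silence of sections 7.1 to 7.3 on analysis sets is therefore no fault. What stands is narrower: the protocol does state a population, twice, and it conflicts with its own rules.

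A reader might infer more than the text supports:

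- *That selection is assigned to the Full Analysis Set.* No section says so. It is only what the literal wording amounts to.
- *That the markers would come from patients without DILI.* Reactivation under an immunosuppressive drug, or injury on top of earlier advanced fibrosis, may be genuinely drug-related. These patients are outside the Main Analysis Set, which is a different matter.
- *That pooling changes which marker is chosen.* This is not shown. ALT and bilirubin would be pooled too, dilution that affects all markers alike need not alter their ranking, and the calculation above includes neither a selection step nor a comparator.
- *That 500 counts suspected cases.* Section 3.1 says "A total of 500 patients with acute DILI will be included" and section 1.6 also speaks of 500 DILI cases. Either could mean included or confirmed patients, and no precision target is missed under either reading.

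**Conclusion.** The concern holds as a contradiction in the current wording about who enters the central analysis. It is clearest for the special groups. For unconfirmed cases it rests on section 5.1 alone.

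The consequence cannot be sized from the protocol. The illustrated range, from 0.75 down to 0.556 or up to 0.784 at shares of 5–30%, depends wholly on assumed shares, recovery rates and marker levels. It includes the case of no change at all. It shows only that pooling cannot be presumed harmless or conservative. Because the wording governs the main output and is cheap to correct, it should be corrected before the analysis population is fixed.

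**What to change.** In sections 1.6.3 and 7, replace the reference to all study data with a statement that selection, AUROC, threshold and Obuchowski analyses use cross-validation, without a hold-out split, on all adjudication-confirmed patients outside the section 3.3 groups. Report those groups separately, as section 3.3 already requires, and use the Full Analysis Set as a sensitivity analysis.

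Reconcile section 1.6.1 in the same amendment, so that confirmed patients who die or withdraw are not dropped from the primary population. Moving the analyses to the Main Analysis Set with section 1.6.1 unchanged would remove all deaths, although mortality is part of recovery category [3] and death of any cause is part of severe clinical DILI (section 6.3.2). At most, section 3.1 should also say whether 500 counts included or confirmed patients.

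The cost is a few sentences, with no extra patients or assays. The analysed set becomes somewhat smaller: 400–450 patients if 500 are included and 10–20% fall outside (an assumed share), with the 5–12% wider intervals shown above.
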